### 2.3. Recruitment and Participants

The protocol includes patients between the ages of 18 and 75 who are assisted at the STDCP, with a diagnosis of cancer pain; who can understand Portuguese, have normal vision and hearing, can move their heads, and have sufficient motor control to perform bodily movements; who have a mobile phone with a compatible system; and who agree to participate in the study and sign the informed consent form (ICF).

Indigenous patients were excluded from study due to cultural peculiarities, language, and special legislation. The other exclusion criteria are patients with a history of serious mental illness (DSM-5, Diagnostic and Statistical Manual of Mental Disorders—schizophrenia, schizotypal disorders, delusional disorders, borderline personality disorder, manic phase in bipolar disorder, and dementia); neurological deficits that compromise the degree of cooperation (Glasgow Coma Scale ≥ 14); impaired comprehension and communication skills based on the researcher’s assessment; reports of discomfort when using immersive virtual reality; disease progression that limits regular outpatient mobility; and patients with brain tumors, brain metastases, metastatic lung neoplasm, or a history of seizures.

In order to participate in the study, patients are required to provide informed consent. The consent document includes a comprehensive explanation of the study’s objectives, its potential risks and benefits, and the various stages of the research process. The subjects are then requested to provide their consent and written informed consent is then obtained from all participants.

The protocol stipulates that harm will be defined if any adverse effect occurs after randomization of study participants. The harm will be evaluated systematically at all time points of the study (T1, T2, T3) through the use of structured questionnaires and symptom scales, as well as non-systematically through spontaneous reports from participants. All events will be documented, and serious adverse events will be reported to the ethics committee, as required by Brazilian ethical standards. The ICH Good Clinical Practice (ICH-GCP) definitions will be used to categorize all adverse events.

The protocol does not utilize an Independent Data Monitoring Committee, as this randomized controlled protocol uses non-invasive behavioral interventions (guided meditation via virtual reality, video, or audio) and does not include any procedures or treatments associated with significant safety concerns or potential for adverse events. Therefore, it is not expected to cause serious adverse events.

The responsibility for conducting safety monitoring lies with the research team, in accordance with the Good Clinical Practice guidelines. The nature of the study does not permit interim analyses; consequently, there is no definition of early termination guidelines or statistical stopping rules. Consequently, preliminary data analyses will not be disseminated to members of the research team or to external parties.

In accordance with the principles of ethics and regulatory compliance, the dissemination of anonymised individual participant data is strictly prohibited, and the publication of study results will be limited to a purely aggregated form. It is important to note that the study may be terminated prematurely in the event of any unforeseen safety concerns or at the discretion of the Research Ethics Committee. In such cases, the ultimate decision shall be made by the principal investigator, following consultation with the ethics committee.

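### The Glasgow Coma Scale cut-off in the exclusion list (≥ 14) contradicts the criterion it is attached to and the inclusion criteria

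*Protocol article*

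**What the plan says.** Section 2.3 (Recruitment and Participants) of the protocol article gives the inclusion criteria and then the exclusions.

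- **Inclusion.** Participants are those "who can understand Portuguese, have normal vision and hearing, can move their heads, and have sufficient motor control to perform bodily movements", and "who agree to participate in the study and sign the informed consent form (ICF").
- **Exclusion.** After a separate sentence on Indigenous patients, the list begins "The other exclusion criteria are patients with a history of serious mental illness". One of its items is "neurological deficits that compromise the degree of cooperation (Glasgow Coma Scale ≥ 14").
- **Neighbouring exclusions.** The same sentence also excludes "impaired comprehension and communication skills based on the researcher’s assessment" and "disease progression that limits regular outpatient mobility". Dementia is among the named mental illnesses, and brain tumours, brain metastases and a history of seizures are listed too.

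The Glasgow Coma Scale appears nowhere else in the article. It is not among the instruments in section 2.4 or in Table 2.

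**The concern.** The exclusion item has two parts that point in opposite directions. The words aim at patients who cannot cooperate well enough because of a neurological deficit. The number in parentheses picks out patients at the alert end of the scale.

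An eligibility criterion is meant to be applied as written. If its threshold contradicts its own description, a monitor, an ethics committee or another team cannot tell from the article which rule was applied at screening. That matters more here because section 5 offers the methodology as a reference for later studies.

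**Working it through.** No sample-size or error-rate formula applies. The check is whether the threshold agrees with the words around it.

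**Inputs**

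1. Threshold and direction: ≥ 14 (section 2.3).
2. Where it stands: in the exclusion list (section 2.3).
3. Population wanted: patients who understand Portuguese, see and hear normally, have motor control and sign consent (section 2.3).
4. Assumption, not printed in the article: the scale runs in whole points from 3 to 15, and a higher score means a more alert patient.

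**What the number selects**

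- Possible scores: 15 − 3 + 1 = 13.
- Scores meeting ≥ 14: 15 − 14 + 1 = 2, namely 14 and 15, the top of the scale.
- Scores not meeting it: 13 − 2 = 11, namely 3 to 13.

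**The possible readings**

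| Reading | Excluded by this item | Passed by this item | Agrees with the words and the inclusion criteria? |
|---|---|---|---|
| A. The parenthesis is the rule | Anyone scoring 14 or 15 | Anyone scoring 3 to 13 | No. It removes alert patients. |
| B. Deficit and score both required | Patients with a deficit who score 14 or 15 | Patients with a deficit who score 3 to 13, and everyone without a deficit | No. Among impaired patients, it removes the most alert and passes the less alert. |
| C. ≥ 14 is a level needed for entry | Patients scoring 3 to 13 | Patients scoring 14 or 15 | Yes, but the text states an exclusion and does not say this. |

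Readings A and B keep to the printed text, and both run the wrong way. Reading C is coherent, but only if the number is taken out of the list in which it stands. A reversed inequality would also restore coherence. The article does not show which of these two slips occurred.

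**What the other criteria do**

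A patient at 3 to 13 who passes this item under reading A or B still has to clear "impaired comprehension and communication skills based on the researcher’s assessment", the dementia and mobility exclusions, the language requirement and signed consent. Most patients who cannot cooperate would be stopped there. These criteria cannot undo reading A's other effect: an alert patient excluded by one item stays excluded whatever the others say.

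**What is not touched**

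The sample-size reasoning in section 3.1 and the analysis in section 3.2 do not use the scale. No figure in either section changes.

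**The case against.** The mismatch itself is hard to dispute. The case on the other side concerns its consequences, and much of it stands.

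- **Near-total exclusion.** A reader might infer that almost all of the roughly 140 patients followed monthly (section 3.1) become ineligible, leaving no one to enrol. This needs reading A, which drops the noun of the criterion: a patient with no neurological deficit does not meet the item under reading B, whatever the score. It also needs a distribution of scores among these outpatients, and the article gives none. The 140 is a service caseload and says nothing about scores.
- **Universal deviation.** A reader might infer that every enrolled patient is a protocol deviation. That again depends on reading A. Nothing shown indicates that a score is recorded, and the working eligibility form is not shown.
- **Keeping patients who cannot cooperate.** A reader might infer that the trial admits them. That describes this item taken alone. The neighbouring criteria and the consent requirement would remove most of them.
- **Obvious intent.** The purpose is clear from the criterion's own words, and section 2.2 places screening in a specialist service with doctors on the study team. They are unlikely to apply the item backwards.

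These points limit the practical harm but do not make the criterion correct. This is not a detail that the article left to a fuller document: the article states a threshold, and that threshold contradicts the sentence it belongs to. Relying on staff to disregard the printed sign means that the published rule differs from the one applied.

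**Conclusion.** The point holds as an internal contradiction in a stated eligibility criterion. The cut-off selects the two most alert scores of thirteen, in an exclusion meant for patients with impaired cooperation and beside inclusion criteria that call for patients able to understand, move and consent. Neither reading that keeps to the text rescues it.

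The effect on enrolment cannot be quantified from the article. It ranges from excluding the alert target population (reading A) to a wrong-way item largely covered by other criteria (reading B). The article does not show how the criterion was applied.

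The conclusion rests on one outside assumption, the usual direction and range of the named scale. Randomisation, the primary outcome, the sample size and the analysis are not affected.

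**What to change.** The sponsor should reconcile three things in section 2.3 so that the item excludes patients with impaired cooperation: the wording, the inequality, and its place in the exclusion list. If the sign was reversed, the inequality needs correcting. If ≥ 14 was meant as a requirement for entry, it should be moved to the inclusion criteria or reworded. The choice of cut-off belongs to the sponsor, and none is proposed here.

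The corrected text should say how a score of exactly 14 is treated, because turning the sign round leaves that open. It should also make clear whether the score defines the deficit or is a condition in addition to it.

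The screening form, the ethics submission and the two registry entries named in section 2.2 should be checked for the same error and corrected where it was copied. If the criterion applied at screening differed from the printed one, the report of the trial should state the criterion actually used.

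The cost is a short text correction and an ethics notification. No additional patients, visits or procedures are needed.

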### 2.5. Interventions

The study is conducted at three moments (T1, T2, and T3) with all study groups (case group—Group A; active control group—Group B; passive control group—Group C). In T1 of the study, all groups respond to the baseline assessment approach of the study, which consists of a sociodemographic and clinical questionnaire for the three groups. The data is collected at the FCECON office, immediately after these patients have completed their medical appointment at the Pain Therapy and Palliative Care Service at FCECON.

Participants are randomized into three groups: a case group with guided meditation using virtual reality/3D (three-dimensional) video (Group A), an active control group with guided meditation using 2D (two-dimensional) video (Group B), and a passive control group with guided meditation using audio (Group C). All participants are interviewed at three moments: time 1 (T1)—the first day of intervention and collection of instruments; time 2 (T2)—four weeks after T1; time 3 (T3)—eight weeks after T1.

In all groups and at all moments, T1, T2, and T3, patients respond to the sociodemographic and clinical questionnaire and other instruments measuring quality of life, psychological morbidity, pain, and symptoms. After completing the meditation, patients respond to the Edmonton Symptom Assessment Scale.

The randomization sequence and the type of meditation used in each group at the FCECON office are accessible to the research team, but participants are not aware of the other research groups or the type of meditation is used in each group. Data collection takes place separately on different days and at different times, without one participant having access to another’s meditation.

Subsequently to the in-person intervention at the FCECON office, participants from all three groups receive standardized instructions for conducting home meditation. The practice should be conducted using a video previously provided by the research team, accessed on the participants’ own cell phones, without the need for an internet connection, in offline mode.

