The content of the home meditation consists of the same 2D video with guided meditation audio for Groups A and B and Group C receives only audio for guided meditation. In order to promote adherence to the protocol, all participants receive standardized reminders on their mobile devices requesting that they perform the meditation on Mondays and Thursdays between 9 am and 10 am during the eight weeks of the experimental protocol.

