#### 2.5.1. Case Group (Group A)

This group performs meditation with a virtual reality (VR)/3D (three-dimensional) video: patients watch a 10 min immersive virtual reality video of mindfulness meditation with images and sound in a comfortable chair at the FCECON office, using Samsung^®^ Gear VR virtual reality glasses and a Samsung^®^ smartwatch.

The meditation for Group A consists of watching an immersive 3D virtual reality (VR) video in 360°, entitled “Secret Garden,” where participants can immerse themselves in a beautiful and relaxing Japanese garden, with all the natural elements, such as the flow and sound of running water. This experience was made available by the Italian company BECOME SRL, also known as BECOME. Augmented Life, available at “www.discoverbecome.com”. BECOME SRL is a startup specializing in creating customized virtual reality content and environments for researchers and neuroscientists. The video used in our study was developed especially for this research, with audio in Brazilian Portuguese.

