## Figures and Tables

**Figure 1 healthcare-14-00266-f001:**
[figure not shown]
Flowchart of the experimental design.

**Table 1 healthcare-14-00266-t001:** Temporal implementation of the experimental protocol.

Planning (0–1 Year)	Intervention (1–2.5 Years)
Questionnaire preparation Definition of criteria Patient selection Randomization and sample size Group allocation	Informed consent (TCLE) Initial questionnaire Assessments at 3 time points Meditation protocol Edmonton Symptom Scale

**Table 2 healthcare-14-00266-t002:** Descriptive table of the experimental groups; time of the experimental protocol; and instruments applied.

Group	Time	Study Assessment Instruments
Case group (Group A) Virtual reality/3D (VR)	Time 1 (T1)—First Day of Intervention	
	Before Meditation	Sociodemographic and clinical questionnaire McGill Quality of Life Questionnaire [17] Brief Pain Inventory (Short Form) [18] Hospital Anxiety and Depression Scale [19] The Edmonton Symptom Assessment Scale (ESAS) [20] The National Comprehensive Cancer Network^®^ (NCCN) [21]
	After Meditation	The Edmonton Symptom Assessment Scale (ESAS) [20]
Active Control Group (Group B) Guided Meditation 2D Video	Time 2 (T2)—Four Weeks After T1	
	Before Meditation	McGill Quality of Life Questionnaire [17] Brief Pain Inventory (Short Form) [18] Hospital Anxiety and Depression Scale [19] The Edmonton Symptom Assessment Scale (ESAS) [20] The National Comprehensive Cancer Network^®^ (NCCN) [21]
	After Meditation	The Edmonton Symptom Assessment Scale (ESAS) [20]
Passive Control Group (Group C) Audio-guided meditation—Audio for breathing exercises	Time 3 (T3)—Eight Weeks After T1	
	Before Meditation	McGill Quality of Life Questionnaire [17] Brief Pain Inventory (Short Form) [18] Hospital Anxiety and Depression Scale [19] The Edmonton Symptom Assessment Scale (ESAS) [20] The National Comprehensive Cancer Network^®^ (NCCN) [21]
	After Meditation	The Edmonton Symptom Assessment Scale (ESAS) [20]

**Table 3 healthcare-14-00266-t003:** Overview of outcome measures and analytical framework.

Outcome	Measurement Variable	Analysis Metric	Aggregation Method	Time Points
Primary outcome	BPI: “worst pain in the last 24 h” (0–10)	Change from baseline; final value	Mean (SD); mean difference	T1, T2, T3
Psychological morbidity	HADS total and subscales	Change from baseline	Mean (SD)	T1, T2, T3
Quality of life	McGill Quality of Life Questionnaire scores	Change from baseline	Mean (SD)	T1, T2, T3

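### The VR-discomfort exclusion has no time limit and, for patients new to VR, can be met only after allocation and only in Group A

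*Protocol article*

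**What the plan says.** Section 2.3 (Recruitment and Participants) gives one list of exclusions. After the exclusion of Indigenous patients it continues: "The other exclusion criteria are patients with a history of serious mental illness". Later in the same list come "reports of discomfort when using immersive virtual reality; disease progression that limits regular outpatient mobility". Neither of these two items carries a time point.

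Section 2.3 also covers safety. It says that "harm will be defined if any adverse effect occurs after randomization of study participants", and it commits to documenting all events, with systematic assessment at T1, T2 and T3 as well as spontaneous reports.

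Exposure to VR is described for one arm only. In Section 2.5.1, Group A "patients watch a 10 min immersive virtual reality video of mindfulness meditation with images and sound" at the office. Section 2.5.2 gives Group B a flat video on a phone, and Section 2.5.3 gives Group C audio. Home practice contains no VR: "The content of the home meditation consists of the same 2D video with guided meditation audio for Groups A and B", while Group C has audio alone (Section 2.5). T1, where VR is first used, is "the first day of intervention and collection of instruments".

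**The concern.** An exclusion criterion should be assessable in every candidate before allocation. The VR item is worded as a report made while using VR. Its neighbours on mental illness and seizures are worded as a history, and this item is not. Since the plan describes no VR trial before T1, most patients would have nothing to report until they had been allocated to Group A.

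A criterion that can be triggered only in one arm after allocation gives a licence to remove patients from that arm alone. Staff who know the allocation would apply it: Section 2.5 makes the sequence accessible to the research team, and Section 2.5.4 says the people who set up the equipment and collect the questionnaires know the modality. At stake is the randomized comparison of change in worst pain from T1 to T3. The record of VR tolerability within the analysed group is also affected, and Section 4 says the study will explore whether VR helps adherence and reduces adverse events.

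The progression item has the same gap in timing. Over eight weeks of palliative care, progression is something that can happen to a randomized patient.

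**Working it through.** **Step 1. When and where can each criterion be met?**

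| Criterion | Before randomization | After randomization |
|---|---|---|
| Discomfort when using VR | Only patients who have used VR outside the trial | Group A only (Sections 2.5 to 2.5.3) |
| Progression limiting outpatient mobility | Any candidate | Any arm |

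The wording allows both columns. The asymmetry between arms exists only in the first row, second column.

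**Step 2. What would one-arm removal do?** The plan states no figure on this point, so there is none to reproduce. What follows is an illustration.

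Inputs from the documents: 43 randomized per group and 39 per group before the allowance for loss (Section 3.1); the primary outcome is change in the 0-10 worst-pain item from T1 to T3 (Section 2.6).

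Inputs assumed, because the documents give none: share of Group A removed, p = 5%, 10% or 20%; mean change in those removed worse than in the rest of Group A by D = 1, 2 or 3 points; standard deviation of change 2.5; no other loss.

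If the retained patients have mean change m, the whole arm has (1 - p)m + p(m + D) = m + pD. Analysing only the retained patients therefore shifts the Group A mean by pD in favour of VR.

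With no true difference, the chance of a significant result in favour of A (nominal 2.5%) is about 1 - Φ(1.96 - pD/SE), with SE = 2.5 × √(1/(43(1 - p)) + 1/43).

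Worked case, p = 10%, D = 2: shift = 0.10 × 2 = 0.2; retained = 43 × 0.90 = 38.7; SE = 2.5 × √(1/38.7 + 1/43) = 0.554; 0.2/0.554 = 0.36; 1 - Φ(1.60) = 5.5%.

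| p | Retained of 43 | Shift, D = 1 / 2 / 3 | False-positive rate favouring A |
|---|---|---|---|
| 5% | 40.9 | 0.05 / 0.10 / 0.15 | 3.1% / 3.8% / 4.6% |
| 10% | 38.7 | 0.10 / 0.20 / 0.30 | 3.8% / 5.5% / 7.8% |
| 20% | 34.4 | 0.20 / 0.40 / 0.60 | 5.4% / 10.4% / 18.1% |

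At 20% the arm falls below the planned 39. If D were negative, the same shifts would run against VR. If D were zero, there would be no shift.

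**Step 3. After the correction.** If both criteria act only before randomization, and everyone randomized is followed and analysed as allocated, this source of bias is zero and the rate returns to 2.5%.

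**The case against.** The strongest reply is that this is a recruitment list. Both items sit among entry criteria, and nothing calls them grounds for withdrawal. Both have an ordinary baseline reading: known intolerance of VR, and disease already too advanced for office visits. Table 1 lists "Patient selection Randomization and sample size Group allocation" in that order. No sentence says that a randomized patient leaves follow-up or analysis, and an article may leave the definition of analysis sets to the fuller documents.

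Much of this stands. A reader might infer that the plan removes Group A patients after allocation. The text does not say so; it only fails to rule it out. Table 1 does not settle the matter, because it places group allocation in the planning phase and informed consent in the later intervention phase, so it cannot be read as a sequence for each patient. The baseline reading also leaves the VR item with nothing to act on in patients who have never used VR.

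A reader might also infer that the criterion hides the main harm of VR, or contradicts the harm rule. Neither follows. Section 2.3 requires all events after randomization to be documented, so a removed patient's discomfort should still be on record. No section calls discomfort the main harm. An entry criterion and a harm definition are compatible if the first acts only before randomization.

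Finally, a reader might infer that dropping patients with progression favours VR. Progression can occur in any arm, so nothing in the criterion tilts it that way.

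**Conclusion.** The point holds as a defect in the wording of two criteria, and it matters more for the VR item. Taken literally, that item permits exclusion of randomized patients from Group A alone, by staff who know the allocation. The progression item, if used after randomization, would make the analysed sample selective in all arms.

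The illustrative shift of 0.05 to 0.6 points, with a false-positive rate of 3.1% to 18.1% against 2.5%, rests wholly on the assumed rate, outcome gap and standard deviation. It also assumes that the removed patients are then left out of the analysis. It should not be read as an estimate for this trial. Groups A and B share the home video and VR is confined to the office sessions, so the documents give no ground for saying how patients who are uncomfortable in VR would fare on worst pain at eight weeks. What can be said without those assumptions is that the wording allows a one-arm, post-allocation exclusion, and that closing it costs almost nothing.

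**What to change.** Reword both items in Section 2.3 as conditions assessed before randomization in every candidate: a known history of VR intolerance, and mobility that already limits attendance at screening.

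Add a statement that anyone randomized who later meets either description stays in the allocated arm for analysis, with the T2 and T3 questionnaires still sought, and that discomfort during a VR session counts under the harm rule already in Section 2.3. Whether such a patient continues the intervention is a clinical matter and is not addressed here.

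The cost is two reworded criteria and one added statement. The small downside is that a few patients with incomplete exposure remain in the analysis.
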